## Abstract

**Background:**

Endoscopic hemostasis is used to treat colonic diverticular bleeding (CDB); however, rebleeding is frequently observed after conservative treatment. Currently, evidence regarding the efficacy of oral medications for preventing rebleeding from colonic diverticula is limited. Orengedokuto (Huanglian Jiedu Tang) is a traditional Kampo formula with capillary-constricting and hemostatic properties that are used to treat bleeding conditions such as epistaxis, hematemesis, and melena. If proven to be effective in preventing rebleeding, orengedokuto could reduce the need for hospitalization and repeat endoscopic procedures, thereby lowering the burden on patients and health care systems.

**Objective:**

This study aims to exploratorily evaluate the efficacy and safety of orengedokuto in preventing rebleeding in patients with CDB who have achieved spontaneous hemostasis.

**Methods:**

We designed a double-blind, randomized controlled trial in patients with CDB who achieved spontaneous hemostasis and in whom the bleeding source could not be identified, making endoscopic hemostasis unfeasible. Patient allocation will be determined using a dynamic randomization method based on minimization, with a 1:1 assignment ratio. Treatment will begin within 24 hours of enrollment. The participants will receive either orengedokuto plus standard treatment or placebo plus standard treatment for 14 days, followed by a 31-day observation period. They will take 2 capsules of either orengedokuto or placebo 3 times a day. Standard treatment refers to the standard approach for managing CDB, which involves resting the bowel through fasting and intravenous fluid administration. Corn starch will be used for the placebo. The primary end point is the proportion of patients who experience rebleeding. Secondary end points include the length of hospital stay, time to resumption of oral intake, severity of rebleeding (including the timing of rebleeding and degree of anemia), and incidence of secondary rebleeding. Safety will be assessed through monitoring of adverse events for causality and frequency. For the primary end point, the full analysis set will be used as the analysis population. The proportion of patients with rebleeding will be calculated for each group, and intergroup comparisons will be performed. For the secondary end points, statistical comparisons will be performed between the 2 groups.

**Results:**

This study received funding from the Japan Agency for Medical Research and Development in May 2025. Enrollment is scheduled from July 2025 to December 2027. As of June 2026, we have enrolled 48 participants. All follow-up and data collection activities will be finalized by February 2028. Results are anticipated to be completed in the first quarter of 2028.

**Conclusions:**

If orengedokuto demonstrates a hemostatic effect, it could offer a less invasive alternative to endoscopic hemostasis, potentially reducing hospital stays and overall health care resource use.

## Introduction

The number of patients with conditions that cause acute lower gastrointestinal bleeding (ALGIB) is increasing [1-3]. Recently, colonic diverticular bleeding (CDB) has been reported as the most common cause of ALGIB in Japan [4-6]. The incidence of CDB has increased since 2000, and the number of patients with severe CDB has increased proportionately [3,7]. Endoscopic hemostasis therapy in patients with high-risk stigmata of recent hemorrhage (SRH), including active bleeding, nonbleeding visible vessels, and adherent clots, can prevent recurrent bleeding and decrease the need for surgery [8].

Endoscopic treatment is recommended when active bleeding or SRH occurs, irrespective of etiology [9,10]. Colonoscopy can be used to identify SRH, and endoscopic treatment can suppress rebleeding [8,11-16]. However, SRH is observed in only 8% to 15% of CDB cases [17-19]. In several instances, bleeding stops by the time of colonoscopy; moreover, owing to the presence of numerous diverticula, the rate of identifying the bleeding source is not high. When conservative treatment is administered without endoscopic hemostasis in patients showing signs of bleeding, the early rebleeding rate within 1 month is high (53%‐66%) [8,20].

There is no evidence regarding the effectiveness of pharmacological treatments for hemostasis in cases of diverticular bleeding in which endoscopic hemostasis cannot be performed.

Traditional herbal medicines have long been used to treat various diseases, particularly in Asian countries.

Orengedokuto (Huanglian Jiedu Tang) is a traditional Kampo formula originating from classical Chinese medicine and was first recorded in the ancient medical text Wai Tai Mi Yao [21]. The formula consists of 4 medicinal herbs: Coptidis Rhizoma, Scutellariae Radix, Phellodendri Cortex, and Gardeniae Fructus. Orengedokuto has a long history of use in both Traditional Chinese Medicine and Japanese Kampo medicine to treat heat toxin syndromes, inflammatory conditions, and irritability [21]. It remains the cornerstone formula for clearing internal heat [22]. In Japan, the indications covered by insurance include nosebleeds, hypertension, insomnia, gastritis, dizziness, and palpitations. Orengedokuto is suggested to be involved in primary hemostasis, with potential effects such as vasoconstriction and inhibition of the abnormal activation of the coagulation-fibrinolysis system. Although hemostatic effects on gastrointestinal bleeding are expected, to date, no reports have verified their efficacy. We conducted a retrospective study of patients diagnosed with CDB following colonoscopy at 5 institutions over a 1-year period (January to December 2019; UMIN000049020). We evaluated the rate of rebleeding within 30 days in patients who received conservative treatment because endoscopic hemostasis could not be performed, comparing a group that received orengedokuto with a group that did not. The rate of rebleeding within 30 days was 9.1% (1/11) in the orengedokuto group and 31.1% (15/48) in the control group. Although the difference was not statistically significant (*P*=.26), the rebleeding rate was lower in patients who received orengedokuto. Furthermore, in this study, cases of rebleeding occurred within 10 days.

We designed an exploratory double-blind randomized controlled trial to investigate the efficacy and safety of orengedokuto in preventing rebleeding in patients who experienced spontaneous hemostasis after CDB and in whom the bleeding source could not be identified, thus precluding endoscopic hemostasis. We hypothesize that adjunctive treatment with orengedokuto will reduce the incidence of rebleeding and improve clinical outcomes without compromising safety compared with placebo.

## Methods

### Study Design

In this double-blind, randomized controlled trial, patient allocation will be determined using a minimization-based dynamic randomization method. The stratification factors for allocation are as follows: (1) study site, (2) use of antithrombotic agents (yes/no), (3) history of CDB (yes/no), and (4) age at enrollment (≤69 y/≥70 y). Patients will be assigned in a 1:1 ratio to either the orengedokuto group (orengedokuto plus standard treatment) or the placebo group (placebo plus standard treatment).

The study setting parallels usual practice. Patients will be recruited from the gastroenterology inpatient departments of hospitals in different districts of Japan. A SPIRIT (Standard Protocol Items: Recommendations for Interventional Trials) 2025 checklist is provided in Checklist 1. A flowchart of the study is shown in Figure 1.

**Figure 1. F1:**
[figure not shown]
Study flowchart.

### Ethical Considerations

The study protocol was reviewed and approved by the Institutional Review Board of Kyoto Prefectural University of Medicine (approval number CRB5200001). The trial was registered in the Japan Registry for Clinical Trials (jRCTs051250063) on July 8, 2025. All participants will receive comprehensive study information, including the study’s purpose, potential risks, benefits, and their right to withdraw at any time, and will be required to provide written informed consent before screening. All participants may withdraw from the study at any time without consequence. Participant confidentiality will be ensured by assigning anonymized identification codes. Data are being stored in secure, password-protected databases accessible only to the research team. No personal identifiers will be disclosed in any publication derived from this study. This study is being conducted in accordance with the principles outlined in the Declaration of Helsinki and the Ethical Guidelines for Medical and Biological Research Involving Human Subjects.

The principal investigator (PI) or coinvestigator will select potential participants, confirm that they meet the inclusion criteria and do not meet any of the exclusion criteria, provide written information to potential participants, and obtain written consent.

### Eligibility Criteria

#### Participants

The target condition is CDB with spontaneous hemostasis, where the bleeding source cannot be identified during endoscopy; hence, endoscopic hemostasis cannot be performed. Confirmed CDB was defined as the presence of SRH within a diverticulum on colonoscopy. Suspected CDB was defined as either contrast-enhanced computed tomography demonstrating contrast extravasation localized to a diverticulum without the subsequent endoscopic confirmation of SRH or the absence of SRH on colonoscopy, despite reasonable exclusion of other causes of lower gastrointestinal bleeding, making diverticular bleeding the most likely diagnosis. We set the inclusion criteria as a colonoscopy performed within 24 hours of the initial visit. The reason for this was that this study focused on patients with colonoscopically confirmed diverticular bleeding, and we prioritized the internal validity of the study by enhancing diagnostic accuracy.

Patients are required to meet all of the following inclusion criteria and none of the exclusion criteria.

#### Inclusion Criteria

The inclusion criteria are as follows:

Patients aged 18 to 89 years at the time of providing informed consent.Patients who present to the hospital within 48 hours of the onset of hematochezia. A colonoscopy was performed within 24 hours of the initial visit, and the patient was diagnosed with diverticular bleeding; however, because no SRH (active bleeding, nonbleeding visible vessels, and an underlying adherent clot with active bleeding or nonbleeding visible vessels) was detected, endoscopic hemostasis could not be performed, and the bleeding has since stopped spontaneously.Patients who experience dizziness or palpitations.Hospitalized patients with a shock index [23] of less than 1.0.Patients who have been adequately informed about the study, have fully understood the explanation, and have voluntarily provided written informed consent.

#### Exclusion Criteria

The exclusion criteria are as follows:

Patients in whom the responsible diverticulum could not be identified through colonoscopy and were scheduled to undergo emergency surgery, transarterial embolization, or barium enema therapy due to ongoing bleeding;Patients with a history of colorectal resection (excluding appendectomy);Patients who have received orengedokuto (Huanglian Jiedu Tang) within 2 weeks prior to colonoscopy;Patients with a history of CDB within 30 days prior to colonoscopy;Patients in whom the cecum could not be visualized during colonoscopy;Patients with severe organ dysfunction defined as follows (laboratory tests within 4 weeks prior to treatment are acceptable):Renal function: serum creatinine level 1.5 times more than the normal threshold for the institution;Hepatic function: serum aspartate aminotransferase or alanine aminotransferase levels more than 3 times the normal threshold for the institution; andElectrolytes: serum sodium level of less than 125 mEq/L or serum potassium level of less than 3.3 mEq/L.Women who are pregnant or breastfeeding, who may be pregnant, or who are planning to conceive;Patients with a history of allergy to orengedokuto;Other causes of gastrointestinal bleeding identified during colonoscopy, such as advanced colorectal cancer, ulcerative colitis, Crohn's disease, or infectious colitis;Patients who are currently participating in, or intend to participate, in another clinical trial during the study period; andAny other patients whom the PI or subinvestigator deems unsuitable for participation in the study

### Interventions

Both groups will receive standard treatment (bowel rest through fasting and intravenous fluid administration), which is the standard treatment for CDB. When comparing the orengedokuto group with the placebo group, the only difference between the test groups will be the presence or absence of the active ingredient in the intervention being tested. There is no available treatment for CDB; hence, there is no inherent disadvantage of using a placebo. Moreover, the placebo effect can be controlled by using a placebo as the test drug for the placebo group.

The intervention will commence within 24 hours of registration. Based on the allocation results, patients will receive either orengedokuto (orengedokuto plus standard treatment) or placebo (placebo plus standard treatment) for 14 days. Patient registration will be conducted through a web-based registration and allocation system managed by the data center. An interactive web system will ensure that the allocation remains concealed until it is assigned. The allocation sequence will be computer-generated and allocated using the interactive web system. Investigators or subinvestigators at each participating site will access the registration system via its URL to complete registration and obtain allocation results.

Subsequently, an observational follow-up will be conducted for 31 days from the start of treatment. Standard care refers to fasting and bowel rest, which are routinely used to treat CDB.

Orengedokuto is a traditional herbal medicine used in Japan. Each dose (6 capsules) contains the following herbal ingredients: ogon (3.0 g), oren (1.5 g), sanshishi (2.0 g), and obaku (1.5 g). Regarding the dosage, in accordance with insurance coverage guidelines, the recommended regimen is 2 capsules 3 times daily. Therefore, patients will take 2 capsules of either orengedokuto or placebo 3 times a day. As our retrospective analysis found that cases of rebleeding occurred within 10 days, we have set the treatment duration to 14 days. This study is being conducted using the investigational drug, orengedokuto, and a placebo both provided free of charge by Kotaro Kampo Pharmaceutical Co, Ltd. The placebo contains corn starch as the inactive filling material and was manufactured and supplied by Kotaro Kampo Pharmaceutical Co, Ltd. The placebo capsules were designed to be indistinguishable from the active capsules in appearance, shape, labeling, packaging, and administration schedule.

Blood tests, confirmation of hematochezia, and physical examinations will be performed prior to enrollment and on the day after the intervention. During hospitalization, daily assessments for hematochezia and physical examinations will be performed. On day 15 of the intervention, blood tests, confirmation of hematochezia, and physical examinations will be repeated. On day 31, confirmation of hematochezia and physical examinations will be conducted. Figure 2 shows the participants’ timelines.

All patients with ALGIB undergo colonoscopy for diagnosis and treatment within 24 hours of admission. Patients will be administered hypertonic polyethylene glycol solution (1‐2 L) for bowel preparation, except for those with contraindications. Patients with hemodynamic instability will be administered enemas.

**Figure 2. F2:**
[figure not shown]
Schedule of enrollment, interventions, and assessments.

### Criteria for Discontinuing or Modifying Allocated Interventions

The PI or subinvestigator shall discontinue the investigational drug and terminate the patient’s participation in the study if it is determined, for any of the following reasons, that continued participation is not feasible. In such cases, the reason for discontinuation will be explained to the study participants, as necessary. Furthermore, the postdiscontinuation treatment will be handled sincerely to avoid any disadvantages to the participant.

Discontinuation criteria are as follows:

If the participant withdraws consent to participate in the study;If it is found after enrollment that the participant does not meet the eligibility criteria (inclusion/exclusion criteria);If the underlying disease worsens and continued administration of the investigational drug is deemed inappropriate;If complications worsen and make it difficult to continue the study;If it becomes difficult to continue the study owing to adverse events;If the participant is found to be pregnant;If the participant exhibits extremely poor adherence, such that medication compliance is objectively deemed to be below 70%;If the underlying disease is completely cured and continued administration is no longer necessary;If the entire study is discontinued; andIf the investigator otherwise deems it appropriate to discontinue the participant’s involvement in the study for any other reason.

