### Data Collection and Management

The PI or subinvestigator at each participating medical institution will promptly complete a CRF after collecting the specified tests and evaluation items. In this study, paper-based CRFs will be sent to the data center via fax. Data will be entered directly into a database managed by the data center.

Participants who do not attend their scheduled visits will be contacted by phone. Follow-up will be continued regardless of protocol adherence.

The PI will appoint a data management supervisor to oversee and coordinate the timely creation of CRFs and data collection to ensure the development of an appropriate dataset. The data management supervisor will be responsible for monitoring the progress of CRF completion and data entry, as well as for conducting data review and cleaning. Furthermore, the data management supervisor will be accountable for the quality of the datasets used in the analysis.

The PI will also appoint a monitoring officer to conduct central monitoring to ensure that the study is being conducted safely and in accordance with the study protocol, the Clinical Research Act, and other applicable regulations and that the data are being accurately collected. The monitoring officer will report the results to the PI.

Personal information in the database will be password-protected on a secure network. No identifying information will be used in any analysis, report, or publication. Biological specimens for genetic or molecular analysis will not be collected in this study.

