### Statistical Methods

The full analysis set (FAS) will include all enrolled participants, excluding those who are found to be ineligible, those who do not receive any study treatment after enrollment, and those for whom no postenrollment measurements are available. The per-protocol set will include participants in the FAS, excluding those for whom the primary outcome is not evaluable and those with major protocol deviations, such as incorrect treatment allocation, use of prohibited concomitant treatments, or treatment adherence of 70% or less. The safety analysis set will include all enrolled participants who receive at least one dose of the study treatment.

For the primary end point, the FAS will be used as the analysis population. The proportion of patients with rebleeding will be calculated for each group, and intergroup comparisons will be performed using Fisher exact test, consistent with the method used for sample size calculation. A 2-sided significance level of 5% will be applied. Additionally, a sensitivity analysis will be conducted using the per-protocol set to assess the robustness of the results.

For the secondary end points, the FAS will also be used as the analysis population. Statistical comparisons will be performed between the 2 groups for the following variables:

Mean duration of hospitalization;Mean number of days until the initiation of oral intake;Severity of rebleeding (including timing and degree of anemia); andProportion of patients with recurrent rebleeding (re-rebleeding)

The Wilcoxon rank-sum test will be used to analyze continuous variables. Fisher exact test will be used to analyze categorical variables. No adjustment for multiplicity will be made for the secondary end point analyses, which will be considered exploratory. Further details will be prespecified in the statistical analysis plan, which will be finalized before database lock and unblinding.

The safety analysis set will be used for the safety analysis. Safety will be evaluated separately for the treatment and follow-up periods. Adverse events will be assessed in terms of type, frequency, severity, and causal relationship with the investigational drug. The incidence rates of adverse events will be calculated and compared between groups. If statistical testing is applied, the Fisher exact test will be used for comparison.

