No interim analyses are planned. Missing data will not be imputed and will be treated as missing in the analysis. If missing data are expected to affect outcomes, sensitivity analyses will be planned and conducted accordingly. All sensitivity analyses will be prespecified prior to database lock.

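### The discontinuation rule ends study participation along with study drug, conflicts with the follow-up promise for poor adherers, and can leave 30-day outcomes uncollected that the primary analysis then omits

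*Protocol article*

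**What the plan says.** **Stopping rule** (Protocol article, Criteria for Discontinuing or Modifying Allocated Interventions). The operative sentence reads "The PI or subinvestigator shall discontinue the investigational drug and terminate the patient’s participation in the study". It applies when it is determined, "for any of the following reasons, that continued participation is not feasible". The listed reasons include that "medication compliance is objectively deemed to be below 70" percent, and "If the underlying disease worsens and continued administration of the investigational drug is deemed inappropriate". Adverse events that make continuing difficult, complete cure and the investigator's general judgement are also listed, as are consent withdrawal and closure of the whole study. The section describes no status in which a patient is off drug but still followed.

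**Follow-up rule** (Data Collection and Management). "Follow-up will be continued regardless of protocol adherence".

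**Analysis rules** (Statistical Methods). "For the primary end point, the FAS will be used as the analysis population". The FAS leaves out ineligible patients, untreated patients and those with no measurement after enrollment; discontinuation is not an exclusion. On missing values: "Missing data will not be imputed and will be treated as missing in the analysis". The next sentence adds: "If missing data are expected to affect outcomes, sensitivity analyses will be planned and conducted accordingly", to be fixed before database lock. The one sensitivity analysis named for the primary end point uses the per-protocol set, which also leaves out patients whose primary outcome cannot be evaluated.

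**Time frame.** Treatment runs 14 days (Interventions). Rebleeding is counted over 30 days from enrollment (Primary End Point). The day-31 check may be made by telephone (Strategies to Improve Adherence to Interventions).

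**The concern.** Two operative rules give sites opposite instructions for the same patient. A site that follows the stopping rule closes the patient's record; a site that follows the data collection rule keeps calling. Whether a 30-day outcome exists could then depend on which section the site read.

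This matters because several reasons for termination are plausibly linked to prognosis or to treatment: worsening, cure, adverse events, poor adherence. If patients leave for such reasons and their outcomes are not collected, the comparison among those with known status need not equal the comparison among those randomised. Terminating poor adherers also pulls the FAS result toward the per-protocol result. A later analysis plan can choose how to handle missing outcomes, but it cannot recover outcomes that sites stopped collecting. Enrollment is open, with 48 of 120 enrolled as of June 2026.

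**Working it through.** **Step 1. Compare the rules, reason by reason.**

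| Reason in the stopping rule | Against the follow-up rule |
|---|---|
| Compliance below 70% | Direct conflict: that rule speaks of protocol adherence |
| Adverse events, worsening, cure, investigator judgement | Less direct: these are reasons about the drug or the disease, and outcome collection would usually still be possible |
| Consent withdrawn, whole study closed | No conflict |

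**Step 2. Trace a patient to the primary analysis.** Take a treated patient terminated during the 14-day course with no rebleed so far.
- At least 30 − 14 = 16 of the 30 days are unobserved, which is more than half the window.
- The patient has a measurement after enrollment, so remains in the FAS.
- If 30-day status is unknown it is treated as missing, so the patient cannot be placed in either row of the 2×2 table.
- The per-protocol analysis excludes the patient too, so it does not test the effect of this loss.

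A patient whose rebleed was recorded before termination still counts as an event.

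**Step 3. Reproduce the plan's sample size.** Inputs (Sample Size): 31.3% vs 9.1%, two-sided 5%, Fisher exact test, power at least 80%. Exact power is the sum, over all pairs of event counts (i, j) with Fisher p ≤ 0.05, of Bin(i; n, 0.313) × Bin(j; n, 0.091).
- n = 56 per arm: 79.3%
- n = 57 per arm: 80.3%

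The stated 57 per group reproduces. Enrollment of 120 gives 60 per arm, an allowance of 60 − 57 = 3 per arm (6/120 = 5%), which must also cover ineligible cases.

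**Step 4. Size the loss of information.** The documents give no termination rate, so the losses below are assumptions, equal in both arms and unrelated to outcome.

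| Assumed loss | Evaluable per arm | Exact Fisher power |
|---|---|---|
| 0% | 60 | 82.6% |
| 5% | 60 × 0.95 = 57 | 80.3% |
| 10% | 60 × 0.90 = 54 | 77.3% |
| 15% | 60 × 0.85 = 51 | 75.6% |
| 20% | 60 × 0.80 = 48 | 71.8% |

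**Step 5. Show how far unknown outcomes could move the result.** Suppose 6 patients per arm are terminated and the known cases are 17/54 (placebo) and 5/54 (active): Fisher p = 0.008. Filling in the 12 unknown outcomes gives:

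| Rebleeds among the 6 unknown (placebo, active) | Counts | p |
|---|---|---|
| 2, 1 (planned rates give 6 × 0.313 = 1.9 and 6 × 0.091 = 0.5) | 19/60 vs 6/60 | 0.006 |
| 2, 2 | 19/60 vs 7/60 | 0.014 |
| 2, 3 | 19/60 vs 8/60 | 0.028 |
| 0, 3 | 17/60 vs 8/60 | 0.07 |
| 0, 6 | 17/60 vs 11/60 | 0.28 |

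In this example the conclusion is stable unless the unknown outcomes are strongly adverse to the active arm. The last two rows are stress cases, not forecasts.

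**The case against.** The strongest reply is that the stopping rule is conditional. It applies only when continuing is judged not feasible; worsening counts only if further drug is deemed inappropriate, and adverse events only if they make continuing difficult. That stands: termination is not automatic, and the direct clash is confined to the adherence criterion. It does not remove the problem, since low compliance or a reason for stopping capsules does not by itself make a telephone call infeasible.

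Second, a reader might infer that discontinued patients are dropped from the primary analysis as a group. The documents do not support that. Discontinuation is not an FAS exclusion and recorded rebleeds count; only those terminated without a recorded rebleed and with unknown later status are affected.

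Third, the plan provides for further sensitivity analyses before database lock and leaves details to an analysis plan that is not shown. The absence of a tipping-point table from the article is therefore not itself a fault. The provision is conditional, however, and leaves the primary analysis unchanged.

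Fourth, the sponsor's retrospective rebleeds occurred within 10 days, so terminations late in the treatment course may cost few events. That is fair, though it rests on 16 rebleeds (1 + 15) and does not cover early terminations.

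Finally, one might infer that patients who rebleed are terminated and so cannot contribute to the recurrent-rebleeding end point. Rebleeding is not a listed reason; it would end participation only if judged to meet the worsening or general-judgement criterion.

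**Conclusion.** The point holds in a limited form. The two sections contradict each other for patients below 70% compliance, and the stopping rule also ends follow-up for other drug-related reasons where the outcome could usually still be obtained. Patients terminated without a recorded rebleed and with unknown 30-day status fall out of both the primary Fisher comparison and the per-protocol analysis.

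The size cannot be fixed from the documents because no termination rate is given. Under assumed, non-informative losses of 10% or 15%, power is 77.3% or 75.6% instead of 80.3%, a modest cost. Possible bias is the greater worry, but its direction and amount are unknown. It would be tempting to say that the primary contrast is no longer a randomised comparison, or that a significant result would be overturned. Neither follows: the first depends on an unknown number of such terminations, and the second needs the extreme patterns in the last two rows of step 5. The sample size of 57 per group is not in dispute.

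**What to change.** Reconcile the two sections by separating the end of study drug from the end of follow-up.

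1. Leave the drug-stopping criteria as they stand; no view is taken on them. State that stopping the drug does not end follow-up.
2. Collect hematochezia status through day 31 for every randomised patient unless consent to follow-up is withdrawn or the patient dies. The existing telephone option serves for this.
3. Keep the Fisher test in the FAS as the primary analysis. Prespecify a tipping-point sensitivity analysis for patients whose 30-day status is still unknown.

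A change of primary estimator is not needed and would not solve the problem: Kaplan-Meier assumes non-informative censoring, and counting events up to last contact treats unknown outcomes as event-free.

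The cost is a short protocol amendment, a paragraph in the analysis plan and a few extra telephone contacts. It should be made while enrollment is open, because outcomes not collected now cannot be recovered at database lock.
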